## Abstract

**Background:**

The criminal justice system is the largest provider of mental health services in the USA. Many jurisdictions are interested in reducing the use of the justice system for mental health problems. The national Stepping Up Initiative helps agencies within counties work together more effectively to reduce the number of individuals with mental illness in jails and to improve access to mental health services in the community. This study will compare Stepping Up counties to matched comparison counties over time to (1) examine the effectiveness of Stepping Up and (2) test hypothesized implementation mechanisms to inform multi-agency implementation efforts more broadly.

**Methods:**

The study will survey 950 counties at baseline, 18 months, and 36 months in a quasi-experimental design comparing implementation mechanisms and outcomes between 475 Stepping Up counties and 475 matched comparison counties. Surveys will be sent to up to four respondents per county including administrators of jail, probation, community mental health services, and community substance use treatment services (3800 total respondents). We will examine whether Stepping Up counties show faster improvements in implementation outcomes (number of justice-involved clients receiving behavioral health services, number of behavioral health evidence-based practices and policies [EBPPs] available to justice-involved individuals, and resources for behavioral health EBPP for justice-involved individuals) than do matched comparison counties. We will also evaluate whether engagement of hypothesized mechanisms explains differences in implementation outcomes. Implementation target mechanisms include (1) use of and capacity for performance monitoring, (2) use and functioning of interagency teams, (3) common goals and mission across agencies, and (4) system integration (i.e., building an integrated system of care rather than adding one program or training). Finally, we will characterize implementation processes and critical incidents using survey responses and qualitative interviews.

**Discussion:**

There are few rigorous, prospective studies examining implementation mechanisms and their relationship with behavioral health implementation outcomes in justice and associated community behavioral health settings. There is also limited understanding of implementation mechanisms that occur across systems with multiple goals. This study will describe implementation outcomes of Stepping Up and will elucidate target mechanisms that are effective in multi-goal, multi-agency systems.

**Supplementary Information:**

The online version contains supplementary material available at 10.1186/s13012-021-01095-2.

Contributions to the literature
This paper describes the methods for the first prospective national study evaluating implementation outcomes of efforts to help justice and community behavioral health systems work together better to keep individuals with mental illness out of jail.This protocol paper provides an example of how to study outcomes and mechanisms of policy implementation.This protocol paper provides an example of a strong quasi-experimental design that allows for testing both implementation outcomes and mechanisms when randomization is not possible, which is often the case with policy implementation.The quasi-experimental design is especially strong and the sample large (950 counties) for a policy implementation research study, a still understudied area of implementation science.

## Background

More than 10 million adults are arrested and enter the United States criminal justice (CJ) system, including pretrial detention, jail, probation, and parole, each year [1]. Rates of current mental health (56%) and substance use (66%) disorders are elevated among justice-involved populations [2], who disproportionately lack education, experience victimization and homelessness, and have poor employment skills, complicating care and increasing morbidity and mortality [3–13]. The CJ system is a low-resource setting charged with serving people who face complex behavioral and physical health issues, with inadequate access to health care.

Counties (which often operate jails, probation and/or parole services, community mental health, and substance use treatment systems) care for the vast majority of justice-involved individuals. Recognizing that counties are overwhelmed by overuse of incarceration for those with mental health and substance use disorders and by the lack of health services for justice-involved individuals in the community, the National Association of Counties (NACo), the Council of State Governments (CSG) Justice Policy Center, and the American Psychiatric Association Foundation (APAF) developed the Stepping Up Initiative [14]. The goal of Stepping Up is to reduce the number of individuals with serious mental illness in jails and to improve access to community mental health services for currently or potentially justice-involved individuals. To join Stepping Up [14], counties pass a resolution to reduce unnecessary use of jail and increase access to community behavioral health services using a broad, locally adaptable six-step action plan: (1) convene a diverse team of leaders, (2) collect and review data on individuals in the justice system, (3) examine treatment and service capacity, (4) develop a plan with measurable outcomes, (5) implement the plan, and (6) track ongoing progress with data. Since it began in 2015, Stepping Up has registered more than 500 counties.

This study will compare implementation outcomes and mechanisms in the first 475 Stepping Up counties to those in 475 matched comparison counties to: (1) examine the effectiveness of Stepping Up and (2) test hypothesized implementation mechanisms to inform multi-agency implementation efforts more broadly. The study team did not design Stepping Up. However, the national Stepping Up effort provides a unique opportunity for a strong quasi-experimental study examining multi-agency implementation outcomes and mechanisms hypothesized to lead to these outcomes.

## Definitions

This study uses a broad definition of mental health and substance use evidence-based practices and policies (EBPPs) including (1) behavioral and pharmacological treatments; (2) procedures such as assessment and care coordination; (3) practices such as diversion, supported employment, and problem-solving courts; and (4) policies including laws or regulations, judicial decrees, and agency guidelines. Our definition of “justice-involved individuals” is taken from the Sequential Intercept Model [15], and includes the full range of relevant county and local justice involvement (i.e., 911 calls, local law enforcement contact, pretrial jail detention, court appearances, specialty courts, jail sentences, probation, and parole). Implementation outcomes include number of justice-involved clients receiving behavioral health services, number of behavioral health EBPP available to justice-involved individuals, and resources for behavioral health EBPP for justice-involved individuals.

## Implementation mechanisms

Recent work has emphasized the importance of identifying implementation mechanisms underlying observed implementation outcomes [16]. Identifying implementation mechanisms can inform future development of more powerful implementation interventions. Lewis et al. define implementation mechanisms as “processes or events through which an implementation strategy operates to effect desired implementation outcomes” (p.3) [16]. Mechanisms examined in this study come from the Criminal Justice Interagency Implementation Model (CJ-IIM; Fig. 1) [17], which describes the need for cooperation of multiple constituencies for CJ to pursue public health goals (such as improving mental health and substance use services). Implementation mechanisms described in the CJ-IIM address the cross-contextual-layer cooperation needed for behavioral health implementation in CJ systems. This study proposes to examine four of the CJ-IIM mechanisms (performance monitoring, interagency work groups, goal and mission setting across agencies, and system integration) as mechanisms of action for Stepping Up (Table 1).

**Fig. 1 Fig1:**
[figure not shown]
Study implementation mechanisms are taken from the Criminal Justice Interagency Implementation Model (IIM). Figure adapted from Taxman et al. [17]

**Table 1 Tab1:** Study constructs, function, relation to Stepping Up, and relation to the study conceptual model (CJ-IIM)

Construct	Study function	Relation to Stepping Up	CJ-IIM concept
**Target implementation mechanisms**			
Use of/capacity for performance monitoring	Mechanism	Steps 2, 3, and 6: Collect, measure and track capacity	Performance monitoring
Use and functioning of interagency teams	Mechanism	Step 1: Convene a diverse team of leaders	Interagency workgroups
Common goals and mission across agencies	Mechanism	Steps 4 and 5: Develop and implement a plan together	Goal, mission setting
System integration (vs. single programs)	Mechanism	Steps 4 and 5: Develop and implement a plan together	System of care
**Implementation outcomes**			
Number of justice-involved clients who received behavioral health services	Primary	Outcomes are indicators of county capacity to identify and treat justice-involved individuals with behavioral health problems and link them to or provide appropriate community care.	
Number of behavioral health EBPP available	Secondary		
Resources for behavioral health EBPP	Secondary		

### Use of and capacity for performance monitoring

Performance monitoring refers to the use of data to assess population needs, understand how systems work, identify desired outcomes, and monitor progress. Stepping Up recommends that counties develop capacity for ongoing monitoring of four measures: (1) number of people with mental illnesses who are booked into jail, (2) average length of stay in jail, (3) percent linked to community-based treatment after release from jail; and (4) return to jail rate (i.e., recidivism). Doing so often requires infrastructure development since justice and behavioral health agencies lack common identifiers to track clients across systems, and few jurisdictions have electronic health record systems. This study will assess whether Stepping Up efforts improve counties’ ability to track and use performance monitoring metrics (mechanism) relative to comparison counties, and whether doing so improves implementation outcomes.

### Use and functioning of interagency teams (i.e., mental health, substance use, jail, probation, county government)

Moving away from a focus on one agency to the larger system requires interagency teams to exist and to work together. The failure of agencies to function as a team limits their ability to address larger, system-wide issues. The Stepping Up initiative explicitly promotes an interagency stakeholder model. The first step prescribed by the initiative is for the county to convene a team of jail, probation, community mental health, substance use treatment, and elected representatives to work together on the remaining steps. This study will assess whether Stepping Up efforts improve the use and functioning of interagency teams (mechanism) relative to comparison counties and whether use and functioning of interagency teams improve implementation outcomes.

### Having common goals and mission across agencies

EBPPs are more likely to be implemented in systems with clear, visible goals [18, 19], where the EBPPs are consistent with the agency’s mission [17, 20]. CJ agencies such as jails, police, and prosecutors have primary public safety goals, with some secondary public health responsibilities. For behavioral health EBPP implementation, cooperating systems need to incorporate behavioral health EBPPs as a vital ingredient for achieving the primary mission of public safety or agree that public safety can be better achieved through improved behavioral health [17]. For the systems to work together to address common goals, external stakeholders must support this mission shift. To join Stepping Up, counties pass a resolution providing strong, visible support for health and justice agencies to deviate from their siloed missions to create integrated goals. This study will assess whether Stepping Up increases use of cross-agency goals (mechanism) relative to comparison counties, and whether doing so explains any observed differences in implementation outcomes.

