##### Common goals and mission across agencies (agencies nested within counties)

The primary measure (an adapted NCJTP Goals/Mission scale) [38] assesses each respondent’s perception of the degree to which their agency goals and overall county goals align. Respondents are given a list of goals (e.g., public safety/protection, provide mental health services) and are asked to rank them according to (1) their agency’s priorities and (2) county priorities. A kappa score reflects the degree of consistency between the two lists. The secondary measure, a county-level measure, will be agreement (kappa) among respondents within counties on ratings of the importance of providing mental health treatment services for justice-involved individuals in jail and in the community (separately) on a scale of 1 (unimportant) to 10 (important).

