##### Secondary

We will test the hypothesis that Stepping Up counties will show faster rate of improvement in the *use/functioning of interagency teams* (i.e., total scores on the integrated NCJTP Relationship Assessment Inventory-IOR measure) than control counties using the same statistical techniques. We will test the hypothesis that Stepping Up counties will show faster rate of improvement in *common goals and mission across agencies* (i.e., agreement between perceived agency and county priorities) than comparison counties using GLMM or GEE. We will conduct similar analyses of agreement among respondents within each county on the importance of mental health treatment for justice-involved individuals. We will test the hypothesis that Stepping Up counties will show faster rate of improvement in *system integration* (score of 6 or more on the Relationship Assessment Inventory score) using GEE. Separate secondary analysis will compare rates of change in the use of the same screening and assessment instruments by multiple agencies in Stepping Up and comparison counties.

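### The common-goals mechanism has behavioral health content, but both measures score only agreement, so a slope in kappa alone cannot show whether the mechanism improved

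*Protocol article*

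**What the plan says.** **The mechanism.** The section on having common goals and mission across agencies gives the mechanism content. It says that "cooperating systems need to incorporate behavioral health EBPPs as a vital ingredient for achieving the primary mission of public safety", or alternatively agree that better behavioral health serves public safety. It adds: "For the systems to work together to address common goals, external stakeholders must support this mission shift". The same section also words the mechanism as commonality: "This study will assess whether Stepping Up increases use of cross-agency goals (mechanism) relative to comparison counties".

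**The measures.** Under Aim 1: Target mechanisms, the primary measure asks each respondent to rank a list of goals twice, once for the agency and once for the county. The examples of goals include public safety and mental health services. The score is agreement between the two rankings: "A kappa score reflects the degree of consistency between the two lists". The secondary measure is "agreement (kappa) among respondents within counties on ratings of the importance of providing mental health treatment services for justice-involved individuals", asked separately for jail and community on a 1 to 10 scale.

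**The analyses.** The Secondary paragraph of Aim 1a tests for faster improvement in "agreement between perceived agency and county priorities" and runs similar analyses of the rating agreement. The Secondary paragraph of Aim 1b uses the scores from these measures as mediators. Nowhere does the article analyse the rank given to the behavioral health goals, or the level of the importance ratings.

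**The concern.** Agreement has no direction with respect to what is agreed. The mechanism text describes agencies converging on goals that take in behavioral health, but the score would be just as high if they converged on leaving it out. Aim 1a reads a rise in the score as improvement, and Aim 1b uses the score to explain differences in implementation outcomes.

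At stake is the interpretation of one of the four target mechanisms. A flat slope could coexist with a real shared shift toward behavioral health. A rise could come from agencies lowering behavioral health to match their county. A null mediation result would be equally hard to interpret.

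**Working it through.** The article states no figure for this measure, so there is none to reproduce. The check applies the scoring rule directly.

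**Inputs**
- Two rankings of the same goals per respondent (Aim 1 measures). The number of goals, *n*, is not stated; 6, 8 and 10 are assumed.
- Kappa weighting: not stated; unweighted and quadratic are both shown.
- Ratings from 1 to 10 (Aim 1 measures), with up to four respondents per county (Survey respondents).

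**Step 1: both lists move together.** Identical lists give kappa = 1.00 whatever their order. With mental health services last on both lists, kappa is 1.00. With the goal moved up three places on both, kappa is again 1.00. The change is 0.

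**Step 2: one list moves.** Moving one goal up three places displaces four goals, one by 3 and three by 1.
- Unweighted: observed agreement is (n−4)/n and chance agreement is 1/n, so kappa = (n−5)/(n−1).
- Quadratic-weighted, for two complete rankings: kappa = 1 − 6Σd²/(n(n²−1)), with Σd² = 9+1+1+1 = 12.

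| Goals | Unweighted | Quadratic |
|---|---|---|
| 6 | 1/5 = 0.20 | 1 − 72/210 = 0.66 |
| 8 | 3/7 = 0.43 | 1 − 72/504 = 0.86 |
| 10 | 5/9 = 0.56 | 1 − 72/990 = 0.93 |

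**Step 3: the sign depends on the starting point (8 goals).**

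| Path | Unweighted | Quadratic |
|---|---|---|
| Lists identical; agency raises the goal three places | 1.00 → 0.43 | 1.00 → 0.86 |
| County already three places higher; agency catches up | 0.43 → 1.00 | 0.86 → 1.00 |
| Agency three places higher; agency lowers the goal to match the county | 0.43 → 1.00 | 0.86 → 1.00 |

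The last two paths give the same rise, with opposite meaning for behavioral health.

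**Step 4: effect on a group mean.** If, for illustration, half the agencies followed the first path and the rest did not change, mean kappa would fall by 0.5 × (1 − 0.43) = 0.29 unweighted, or 0.5 × (1 − 0.86) = 0.07 quadratic-weighted.

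**Step 5: the importance ratings.** The table takes four respondents and one item. Agreement *p* is the proportion of the six pairs that match exactly. The kappa shown is unweighted with uniform chance of 1/10, that is (p − 0.1)/0.9.

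| Ratings | Mean | Agreement | Kappa |
|---|---|---|---|
| 1, 1, 1, 1 | 1 | 1.00 | 1.00 |
| 10, 10, 10, 10 | 10 | 1.00 | 1.00 |
| 1, 1, 10, 10 | 5.5 | 2/6 = 0.33 | 0.26 |
| 6, 8, 9, 10 | 8.25 | 0.00 | −0.11 |

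If chance agreement is instead taken from the county's own ratings, kappa is 0/0 (undefined) for both unanimous counties. Either way, the score does not separate all-1 from all-10.

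**The case against.** The strongest reply is that commonality is what the article names. The abstract, Table 1 and the aims all speak of common goals across agencies, and the sentence labelled as the mechanism refers to cross-agency goals. Agreement is therefore a legitimate part of the construct. This stands. A reader might infer that the mechanism is purely a shift toward behavioral health and that agreement is the wrong measure. The article does not support that reading. The fault is only that agreement is scored without the level agreed on.

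A reader might also infer that the score will usually run in the wrong direction. That is not shown either. The falling case needs lists that already agree and an agency that moves before its county. In Stepping Up the county passes a resolution to join, and counties had taken part for 1 to 5 years by study baseline, so an agency catching up, with kappa rising, is at least as plausible. Two of the four respondent roles run behavioral health agencies. Their own lists plausibly put those goals high, so that for them a county moving that way would raise agreement.

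The size is also uncertain: the illustrative group drop of 0.29 becomes 0.07 with quadratic weights. The test and its use as a mediator are both secondary; performance monitoring is primary in each.

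Two replies do not remove the point. The Aim 3 interviews cover 60 of 950 counties and do not change the scored variable. Nor is this simply detail left to a fuller plan, because the article itself fixes agreement as both the score and the tested quantity.

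**Conclusion.** The point holds as a limit on interpretation. The mechanism is described with behavioral health content, while its measures and the analyses built on them see only agreement. Equal low and equal high priority are indistinguishable, a complete shared shift gives zero change, and a one-sided shift can move kappa either way.

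The first two statements follow from the scoring rule for any number of goals and any weighting. The size of a one-sided shift rests on assumptions: for 6 to 10 goals and a three-place move from identical lists, kappa falls to between 0.20 and 0.56 unweighted, or between 0.66 and 0.93 quadratic-weighted. The article gives no basis for saying how many agencies would follow any one path, so no net bias for or against Stepping Up is claimed.

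**What to change.** Keep agreement as the measure of commonality. Add to the Secondary paragraphs of Aim 1a and Aim 1b, from the same survey answers, prespecified companion analyses of:

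- the rank of the behavioral health goals on the agency list and on the county list;
- the county mean, and minimum, of the 1 to 10 importance ratings.

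State that the mechanism will be judged engaged only when agreement is interpreted together with the level agreed on. Priority level should not replace agreement: a mean rating says nothing about commonality, so that would exchange one partial measure for another.

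No new data are needed. The cost is one or two extra secondary tests on bounded or ordinal outcomes, which fit the GLMM and GEE framework already set out under General approaches. The county minimum tends to fall as more respondents answer, so it should be read alongside the number responding.

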### System integration

The CJ-IIM hypothesizes that implementation efforts will be most effective as they broaden engagement and ownership across agencies to develop a county-wide system of care, rather than adding single programs or trainings. Many agencies are involved in CJ behavioral healthcare (e.g., community mental health centers, substance use treatment agencies, police, courts, jail, probation, prison, and parole). Service linkage among them is often inadequate or non-existent [21, 22]. Previous analyses of CJ reform efforts suggest that the tendency is to implement a new program rather than working toward a cohesive system of care [23, 24]. The study will examine whether Stepping Up counties are more successful at creating integrated systems of care (mechanism) than are comparison counties, and whether doing so explains any observed differences in implementation outcomes.

## Implementation mechanisms of Stepping Up (I.M. Stepping Up) study aims

This study will compare Stepping Up counties to matched comparison counties on implementation outcomes and mechanisms (see Table 1). We will use surveys and qualitative interviews to compare 475 Stepping Up and 475 paired target counties at 3 waves: study baseline, 18 months, and 36 months (see Fig. 2). County- and agency-level data will be collected from individuals in 4 specific criminal justice and behavioral health administrator roles in each county (up to 3800 total respondents at each wave). Stepping Up and comparison counties will be compared on rates of change in engagement of target mechanisms (primary) and rates of change in implementation outcomes (secondary). Specific aims are to
*Compare engagement of target implementation mechanisms between Stepping Up and comparison counties.* We will examine whether (a) Stepping Up counties show a faster rate of improvement in hypothesized target mechanisms (use of/capacity for performance monitoring, use and functioning of interagency teams, common goals across agencies, and system integration) than do comparison counties; and (b) whether target mechanisms mediate effects of Stepping Up on implementation outcomes.*Compare implementation outcomes between Stepping Up and comparison counties.* We will examine whether Stepping Up counties show faster rate of improvement in implementation outcomes (number of justice-involved clients receiving behavioral health services, number of behavioral health EBPP available to justice-involved individuals, and resources for behavioral health EBPP for justice-involved individuals) than do comparison counties.*Characterize implementation processes and critical incidents* occurring in Stepping Up and comparison counties. We will (a) use qualitative data to triangulate quantitative findings and enrich an understanding of how the target mechanisms produce outcomes, (b) assess counties’ fidelity to Stepping Up, and (c) explore which naturally occurring implementation strategies used in 950 counties lead to better implementation outcomes.

